
## Objectives

This study will evaluate the efficacy of the Instagram-based vaping cessation intervention among adolescents and young adults in an RCT. The primary aim is to test the efficacy of the intervention to achieve biochemically verified nicotine vaping abstinence when the treatment ends and sustain it for 6 months after the treatment. The secondary aim is to test the effectiveness of the intervention in terms of decreasing vaping frequency, and increasing quit attempts, readiness to quit, confidence in ability to quit, desire to quit, commitment to abstinence, and use of evidence-based cessation strategies assessed immediately, 3 months, and 6 months after the treatment.

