### Inclusion criteria

1. English literacy;2. Age between 13-21 years; 3. Indicate they use social media “most” (≥ 4) days per week; 4. Have vaped at least once per week in the past 30 days; 5. Access to a computer or mobile phone with photo capability to verify abstinence from vaping; 6. Indicate they are considering quitting or are interested in quitting within the next 6 months; 7. Currently reside in California. This is because the funder for this study, the California Tobacco Related Diseases Research Program, requires the research be conducted in California. 

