### Baseline measures

Baseline measures will consist of sociodemographic characteristics, nicotine vaping, quitting experience, motivations to quit (such as readiness to quit vaping, confidence in ability to quit, desire to quit, and commitment to abstinence), other tobacco use, marijuana/cannabis use, social media use integration, and symptoms of depression or anxiety.

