#### Secondary outcomes

We will measure seven secondary outcomes as below:• Vaping reduction by 50% or more between baseline and each follow-up will be calculated at each time point by multiplying the number of vaping days in the past 7 days and the number of puffs or hits they took on an average day. • Vaping quit attempt will be measured by questions asking the presence and the number of quit attempts lasting at least 1 day since the last assessment. • Readiness to quit vaping will be assessed using the Stages of Change Questionnaire [42] to classify participants as in Contemplation or Preparation phases [45]. Outcome will be measured as proportion change in Stage at assessments conducted immediately, 3 months, and 6 months after the treatment. • Confidence in ability to quit will be measured by asking how confident the participants are about avoiding vaping nicotine in the next 6 months. • Desire to quit will be measured by asking how much the participants want to quit vaping. • Commitment to abstinence will be assessed with the Thoughts About Abstinence Form [49], categorizing their goal as no goal, intermediary goal (e.g., reduced vaping), or total abstinence. Outcome will be measured as proportion endorsing a goal of abstinence at each time point. • Use of evidence-based cessation strategies will be measured by asking the supports participants used when they tried to quit in the past (30 days/3 months). 

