#### Secondary analysis

We will estimate and test mixed effects logistic and multinomial regression models for longitudinal ordinal response data to model secondary outcomes for vaping over time: 1) vaping reduction by 50% or more; 2) vaping quit attempts; 3) readiness to quit vaping; 4) confidence in ability to quit; 5) desire to quit; 6) commitment to abstinence (i.e. endorsing the personal goal of wanting to quit nicotine completely); and 7) use of evidence-based cessation strategies.

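### Commitment to abstinence is analysed as follow-up status without the baseline goal that the trial collects, which gives up precision and leaves within-arm proportions unable to show an increase

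*Protocol article*

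**What the plan says.** All references are to the protocol article.

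- **Secondary outcomes.** The Thoughts About Abstinence Form is used for "categorizing their goal as no goal, intermediary goal (e.g., reduced vaping), or total abstinence". The scoring rule follows: "Outcome will be measured as proportion endorsing a goal of abstinence at each time point". The participant's own starting goal plays no part in it.
- **Other outcomes in the same section.** Two are tied to change. One is "Vaping reduction by 50% or more between baseline and each follow-up". For readiness, the rule is "Outcome will be measured as proportion change in Stage at assessments conducted immediately, 3 months, and 6 months after the treatment".
- **Objectives.** The secondary aim is worded as "increasing quit attempts, readiness to quit, confidence in ability to quit, desire to quit, commitment to abstinence".
- **Inclusion criteria, item 6.** "Indicate they are considering quitting or are interested in quitting within the next 6 months".
- **Baseline measures.** These include "motivations to quit (such as readiness to quit vaping, confidence in ability to quit, desire to quit, and commitment to abstinence". Under Study procedure, only people who complete the baseline assessment are randomised.
- **Secondary analysis.** The model statement reads: "We will estimate and test mixed effects logistic and multinomial regression models for longitudinal ordinal response data to model secondary outcomes for vaping over time". No covariates are named. The general Data analysis text adjusts for predictors of attrition. The Primary analysis adds sex and variables related to abstinence.

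**The concern.** The aim is to raise commitment, but the measure records only who holds an abstinence goal at a visit. Entry selects people with some interest in quitting, so a share of them, unknown from the document, will already hold that goal. A follow-up proportion mixes those who kept the goal with those who adopted it, so taken alone it cannot be read as an increase.

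The second cost is statistical. A person's baseline goal probably predicts the later goal. Leaving it out keeps between-person variation in the arm comparison that could be removed at almost no cost. Under the rules the article does state, the baseline goal would enter the commitment model only if it happened to predict attrition.

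**Working it through.** **Inputs from the document.** 234 per group, α = 0.05 and three follow-ups. The 234 was derived for the primary outcome; the article gives no power figure for commitment. It can be reproduced. With 3.2% against 8.3%, two-sided 0.05, 80% power and a pooled variance, one time point needs 326 per group. Multiplying by (1 + (m − 1)ρ)/m with ρ = 0.43 and m = 2 gives 326 × 0.715 = 233.1, so 234. Here 234 serves only as the number per arm.

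**Assumptions.** The article gives neither the baseline share with an abstinence goal nor its correlation with the later goal. I use a correlation r of 0.40, with a range of 0.23 to 0.54, between any two visits including baseline. The article's 0.43 refers to vaping abstinence, so carrying over a similar value is itself an assumption.

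**1. How many follow-up endorsers already held the goal.** If the endorsement rate p is stable, the share is p + r(1 − p). At r = 0.40:
- p = 40%: 0.40 + 0.40 × 0.60 = 64%
- p = 60%: 0.60 + 0.40 × 0.40 = 76%
- p = 80%: 0.80 + 0.40 × 0.20 = 88%

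A second parametrisation lets goals drift. Take baseline share b, retention 0.8 to 0.9 and new adoption 0.2 to 0.3. The share in the control arm is then 53–66% at b = 0.3, 73–82% at 0.5, 86–91% at 0.7 and 96–98% at 0.9.

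**2. Does this bias the comparison?** No. With no treatment effect, retention 0.85 and adoption 0.25, 4,000 simulated trials per setting gave these type I error rates at b = 0.5 / 0.7 / 0.9:
- follow-up only: 0.051 / 0.048 / 0.051
- stratified by baseline goal (Mantel-Haenszel): 0.052 / 0.046 / 0.055

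**3. Precision on the three-visit mean.** Without baseline, the variance of the arm difference is [p₁(1 − p₁) + p₂(1 − p₂)] × k / 234, with k = (1 + 2r)/3. The baseline value removes the fraction r²/k. At r = 0.40, k = 0.60 and the fraction is 0.16/0.60 = 27%. It is 11% at r = 0.23 and 42% at r = 0.54.

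For 60% against 70% at r = 0.40, the variance is (0.24 + 0.21) × 0.60/234, so SE = 0.0340. Power = Φ(0.10/0.0340 − 1.96) = 84%. With baseline, SE = 0.0291 and power = 93%.

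| Difference | r | Without baseline | With baseline |
|---|---|---|---|
| 60% v 70% | 0.23 | 90% | 93% |
| 60% v 70% | 0.40 | 84% | 93% |
| 60% v 70% | 0.54 | 78% | 95% |
| 40% v 50% | 0.23 | 88% | 91% |
| 40% v 50% | 0.40 | 81% | 91% |
| 40% v 50% | 0.54 | 75% | 93% |

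**4. In the kind of model planned.** A random-intercept logistic model was checked by simulation with 234 per arm and a latent correlation of 0.6, which corresponds to an observed correlation of about 0.4. Power rose from about 84% to 93% for 60% to 70%, and from about 83% to 91% for 40% to 50%. Type I error stayed at 5%.

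**5. Where the gain fails.** These figures come from the simulation in step 2, with one follow-up, retention 0.85 and adoption 0.25 in controls.

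| Effect | b | Follow-up only | Stratified by baseline goal |
|---|---|---|---|
| +15 points adoption | 0.5 | 0.38 | 0.49 |
| +15 points adoption | 0.7 | 0.19 | 0.24 |
| +15 points adoption | 0.9 | 0.08 | 0.07 |
| +15 adoption, +8 retention | 0.5 | 0.72 | 0.88 |
| +15 adoption, +8 retention | 0.7 | 0.68 | 0.85 |
| +15 adoption, +8 retention | 0.9 | 0.73 | 0.82 |

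An effect on adoption alone is diluted to 15 × (1 − b) points overall: 7.5, 4.5 and 1.5 points at b = 0.5, 0.7 and 0.9. At 0.9 too few people can change for adjustment to help.

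**The case against.** A reader might infer that the outcome is invalid because most of those counted as successes may never have changed. The document does not support that reading.

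- This is a two-arm randomised comparison, and unchanged endorsers are balanced between the arms. A higher proportion than control is a legitimate reading of increased commitment.
- Keeping an abstinence goal is itself a benefit.
- The article does not label endorsers as responders.
- The entry criterion asks for interest in quitting, which is broader than a goal of total abstinence. An entrant could fall in any of the three goal categories, so a high starting rate is an inference.
- A no-effect follow-up rate need not equal the baseline rate. With retention 0.85 and adoption 0.25, baseline rates of 50%, 70% and 90% become 55%, 67% and 79% with no treatment effect.

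All of that stands. It is also fair that the Secondary analysis text does not say whether baseline is left out of the modelled responses, and that covariates are often settled in an analysis plan, which is not shown here. The point therefore cannot be put as an omission or an error.

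One further objection is that gains computed on a mean of visits do not carry over to a mixed logistic model. The check in that model answers it: the gain was of similar size.

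What remains is that the article fixes a status-only rule for an aim worded as change, and gives a collected, prognostic baseline value no stated use.

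**Conclusion.** The point holds as one of precision and interpretation. Naming the baseline goal in the commitment model would remove about a quarter of the variance at an assumed correlation of 0.4 (11% to 42% over 0.23 to 0.54). That takes power from about 84% to 93% for 60% against 70% at 234 per arm. The gain falls to none when baseline endorsement is near 90% and the effect is only on new adoption. The baseline rates and correlations are assumptions throughout. No gain was computed for readiness, confidence or desire; the same reasoning applies to them.

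The definition is not wrong, the randomised comparison is not biased, and the primary outcome and sample size are unaffected. Severity is minor.

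**What to change.** In Secondary analysis, state that the commitment model includes the participant's baseline abstinence goal (endorsed or not) as a fixed covariate, and that the models for readiness, confidence and desire include their own baseline values.

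Keep the raw proportions at each visit. Beside them, report by arm the baseline proportion with an abstinence goal and, descriptively, new endorsement among those without the goal at baseline and retained endorsement among those with it. State that within-arm proportions alone are not evidence of an increase.

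The cost is one extra model term per outcome and an odds ratio that is conditional on baseline. No new data are needed, since baseline is completed before randomisation. Fixing this in advance also removes a later choice between adjusted and unadjusted results.

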### Data collection and management

The three follow-up assessments conducted immediately, 3 months, and 6 months after the treatment will be administered online using Qualtrics through UCSF MyAccess, which includes Secure Sockets Layer encryption, and adheres to HIPAA standards, allowing encrypted transmission of all survey data. Research staff will send emails, text messages, and messages in Instagram with the survey links to notify participants of assessments. At most three emails will be sent to remind participants of the assessments. Those who don't respond after the three contact attempts are counted as dropout at each time point. Those who don't respond in the previous assessments will still be contacted for later assessments. For instance, a participant who did not do the assessment at 3 months post-treatment will still be notified of the assessment at 6 months post-treatment up to three times. Survey data will be securely transferred to password-protected Excel or SPSS files that will be securely stored online using the UCSF Research Analysis Environment, a secure, HIPAA-compliant desktop environment. Files with identifying information will be stored separately from files with other forms of data. Data will only be accessed by the PI and a research assistant until it is de-identified. Study investigators have completed required UCSF training and certification in the conduct of research with human subjects. All collected data will be analyzed and reported in aggregate form for publications. All survey data collection and storage procedures are consistent with current HIPAA guidelines.

In order to ensure and maintain the scientific integrity of this human subject research project, and to protect the safety of its research participants, we will assemble a Data Safety Monitoring Board (DSMB). The DSMB will meet every six months via video conferencing to review the study protocol and procedures. The DSMB will have the responsibility of assuring that participants are not being exposed to unnecessary or unreasonable risks as a result of the pursuit of the study’s scientific objectives.

### Data analysis

Descriptive statistics will summarize sample characteristics and intervention delivery in each group. We will examine treatment condition and baseline descriptive characteristics as predictors of attrition at intervention end and will control for predictors of attrition as covariates in model testing. Missing data will be minimized through online assessment, and subjects will be re-contacted through social media or email to obtain missing information. Two sets of outcome analyses will be conducted: one self-reported by all participants who are maintained in the study, and another based on biochemically verified abstinence rates.

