Before being able to proceed with the study, participants will indicate on an electronic form that they understand what this study is about, that their participation is voluntary, that they are not required to complete any part of this study, and that there are risks associated with study participation. Incomplete or incorrect answers will result in the potential participant being prompted to review the full consent document before attempting the consent questions again. Potential participants will not be enrolled in the study if they fail to complete the form four times. In both the screening and baseline survey, participants are asked about location questions (zip code in the screening and county in the baseline survey). Our research staff will check the consistency of their answers and contact the participants with inconsistent answers using the contact information they provided to confirm the authenticity of the participants. In addition, participants must follow the study account on Instagram, and study personnel will review the profiles of followers for consistency with age and California location. Irregular or inconsistent answers or participants otherwise having difficulty completing the form will be contacted by trained study personnel who will review the consent material and assist with study enrollment. Study personnel may detect behavior, responses or Instagram accounts that do not appear to be authentic. Fraudulent participants identified through this process will be removed and documented. In the consent form, participants will be asked to remain in the study’s Instagram group throughout the duration of the study (about 7 months) for the intervention and for follow-up contacts. Participants will be paid $10 in the form of an electronic gift card for completing the baseline assessment. Participants will be paid $15–35 for each follow-up assessment for a possible total of $100.

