Participants who sign the consent form will be asked to create a login, and then redirected to the baseline assessment. This study will recruit 500 participants in total. Those completing the baseline assessment are randomized using a computer-generated random sequence which automatically assigns participants without revealing allocation to study investigators. Participants are assigned to either the Instagram intervention or the control condition, which is a referral to free support administered by the California quitline via the website kickitca.org. Approximately two weeks after the first participant is enrolled in an intervention group, the group will begin to receive the intervention program. Groups may start slightly sooner or later than 2 weeks based on the pace of recruitment, aiming for a group size between 5 – 15 participants. Depending on the pace of enrollment, multiple groups may run simultaneously.

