#### Primary analysis

We will use a generalized linear mixed model (GLMM) using the time points immediately, 3 months, and 6 months after the treatment. The model will account for dependence of responses within individuals attributable to repeated measures. GLMMs will include random effects person ID and will be fitted using SAS PROC GLIMMIX with maximum likelihood estimation via adaptive quadrature with a minimum of 15 integration points. Nicotine vaping abstinence will be measured by 7-day point prevalence. Covariates will be sex as a biological variable and other variables that are found to be related to abstinence. If missing data is not negligible, we will use multiple imputation procedures to impute missing data. Data about biochemically verified abstinence will be analyzed using the same method as self-reported 7-day point prevalence of abstinence.

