This intervention is designed for adolescents and young adults, populations in the midst of a stage in life in which they are more susceptible to peer influence [52–54]. Previous studies found that 25% of teenagers aged 16–17 years old posted references to alcohol on their social media profiles [55]; in addition, substance use, violence, sexual behavior, and even suicidality are also commonly displayed on social media platforms [55–58]. This calls for more serious monitoring of daily interaction among the participants in our Instagram groups. First, before starting the groups, we will remind the participants that the focus of the group is on vaping experience and quit vaping efforts, and that interactions should be respectful. Second, we have a trained Guide in the groups, who will monitor the everyday conversation of the participants. If problematic content is spotted, the guide will remind the involved participants privately and report serious cases to the Principal Investigator for resolution and further actions, including study disqualification. One of our inclusion criteria is using social media ≥ 4 days per week. Previous studies have found that depression may be common among adolescents who spend a significant amount of time on online social networks [59]. Another study found that more than half of secondary school students experienced a need for mental health support [60]. Our team is ready to deal with mental health issues and/or with serious withdrawal symptoms such as sleep problems, irritability, or in the unlikely event that they become emotionally distressed as a result of answering assessment questions. The Principal Investigator, a Sub-Investigator, and the Study Physician in this team are all practicing clinicians with experience working with vulnerable populations, young people, and substance use. They can counsel study participants privately over email, or on the phone if necessary and make appropriate referrals to medical providers or mental health resources should participants reveal a need for such support.

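### The self-report analysis covers only a set formed after randomisation, and the conditional imputation rule does not reliably restore the randomised comparison

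*Protocol article*

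**What the plan says.** All references are to the protocol article.

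- **Analysis sets (Data analysis).** There are two outcome analyses: "one self-reported by all participants who are maintained in the study, and another based on biochemically verified abstinence rates". What it means to be maintained is not defined. The section also plans to test treatment condition and baseline characteristics as predictors of attrition at intervention end, to adjust for predictors of attrition, and to re-contact participants for missing information.
- **Missing data (Primary analysis).** "If missing data is not negligible, we will use multiple imputation procedures to impute missing data". No threshold is given. The model is a maximum-likelihood GLMM with a random person effect, fitted to the three post-treatment assessments. Verified abstinence is to be analysed by the same method as self-report.
- **Dropout (Data collection and management).** "Those who don't respond after the three contact attempts are counted as dropout at each time point". Non-responders are still approached for later assessments.
- **Allocation (Study procedure).** "Those completing the baseline assessment are randomized using a computer-generated random sequence which automatically assigns participants".
- **Removal for fraud (Study procedure).** "Fraudulent participants identified through this process will be removed and documented". One of the checks compares location answers: "zip code in the screening and county in the baseline survey".
- **Removal for conduct (Discussion).** If the Guide sees problematic content in the Instagram groups, the Guide is to "report serious cases to the Principal Investigator for resolution and further actions, including study disqualification".

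**The concern.** Randomisation protects the comparison of everyone allocated. It does not protect a comparison of those who remain. If leaving the trial is related both to arm and to continued vaping, the retained groups differ in abstinence even when the intervention does nothing.

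The article gives reasons to take this seriously. Its Discussion reports high dropout and falling engagement in social media interventions. One removal route exists in one arm only, because the control arm is referred to a website and has no monitored group. The rule that could bring lost participants back into the analysis is triggered by a judgement made after the data are seen. At stake are the self-report comparison directly, and the verified comparison through the shared missing-data rule.

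**Working it through.** **1. The plan's own figures.** Sample size estimation gives 234 per group (468), and 500 after 7% dropout. The pooled two-proportion formula for 3.2% against 8.3%, with power 0.80 and alpha 0.05 taken as two-sided (the article does not say), gives 326 per group at one time point. With two repeated measures and rho = 0.43 the factor is (1 + 0.43)/2 = 0.715, and 326 × 0.715 = 233, against the stated 234. For dropout, 468/0.93 = 503, close to 500. Nothing here changes the sample size. What changes is the denominator: 500 randomised (about 250 per arm), against 500 × 0.93 = 465 retained at the planned dropout.

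**2. The sections side by side.**

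- Data analysis limits the self-report set to those retained. Primary analysis allows imputation of missing outcomes. If lost participants are outside the set, there is nothing to impute for them. If they are imputed, the set is not limited to those retained. The two statements need reconciling.
- The GLMM has no baseline outcome among its time points. Someone with at least one follow-up contributes to the likelihood; someone with none contributes nothing unless imputed.
- Under Primary outcome, cotinine kits go only to participants who report abstinence at follow-up and are not using NRT. Survey non-response therefore leaves verified status unknown too, under the same conditional rule.
- Disqualification for group content necessarily follows allocation. The location check uses baseline survey answers, and completing that survey leads to automatic allocation. Removal for fraud may therefore follow allocation, but its timing is not fixed.

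**3. Illustration A: every dropout still vapes, no true effect.** Dropout rates are assumed. With true rate p and dropout d, the retained-only rate is p/(1 − d), and the risk ratio is (1 − d_control)/(1 − d_intervention), whatever p is.

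| Dropout, intervention / control | p | Retained-only rates | Risk ratio | Difference (points) |
|---|---|---|---|---|
| 30% / 15% | 3.2% | 0.032/0.70 = 4.6%; 0.032/0.85 = 3.8% | 0.85/0.70 = 1.21 | 0.8 |
| 40% / 20% | 3.2% | 0.032/0.60 = 5.3%; 0.032/0.80 = 4.0% | 0.80/0.60 = 1.33 | 1.3 |
| 30% / 15% | 8.3% | 0.083/0.70 = 11.9%; 0.083/0.85 = 9.8% | 1.21 | 2.1 |
| 15% / 30% | 3.2% | 0.032/0.85 = 3.8%; 0.032/0.70 = 4.6% | 0.70/0.85 = 0.82 | −0.8 |

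Equal dropout gives a ratio of 1. The last row shows that the bias reverses if the control arm loses more people. With all randomised participants as denominator and dropouts counted as vaping, both arms return to p.

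**4. Illustration B: retention depends on outcome in one arm.** Control retains 90% of everyone. Intervention retains 90% of abstainers and a fraction r of the others. The retained-only intervention rate is 0.9p/(0.9p + r(1 − p)).

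- p = 3.2%, r = 0.70: 0.0288/(0.0288 + 0.6776) = 4.1%, against 3.2% in control.
- p = 3.2%, r = 0.60: 0.0288/(0.0288 + 0.5808) = 4.7%, against 3.2%.
- p = 8.3%: 10.4% (r = 0.70) or 12.0% (r = 0.60), against 8.3%.

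**5. Disqualification alone.** With 250 × 0.032 = 8 abstainers, removing 5, 10 or 25 non-abstainers gives 8/245 = 3.3%, 8/240 = 3.3% or 8/225 = 3.6%, against 8/250 = 3.2%. Outcome-related dropout is the larger risk.

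**The case against.** The strongest reply is that the restriction is worded for self-report, whereas the abstract names biochemically verified abstinence as the primary outcome. Being maintained may mean only not withdrawn or removed, since dropout is counted per assessment and non-responders are approached again. The analysis has several safeguards: a likelihood-based mixed model that uses all available follow-ups, adjustment for predictors of attrition, re-contact, imputation, and a check of whether arm predicts attrition. Details of imputation normally belong in the analysis plan, which is not shown. The dropout gaps above are assumed, ignore these safeguards, and yield 0.8 to 1.3 points at 3.2%, against a planned difference of 8.3 − 3.2 = 5.1.

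Much of this stands, and it rules out several stronger readings that a reader might infer:

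- That the verified analysis is itself restricted to those retained. The article does not state its population; it shares the method and the conditional rule.
- That imputation is the only safeguard, or that unequal dropout would go unnoticed. The measures just listed contradict both.
- That fraud removals do follow allocation, or fall more heavily on the intervention arm. The timing is open, the location answers precede allocation, and the profile review is described for followers of the study account generally. Removing false entries blind to arm on such data is defensible.
- That the bias must favour the intervention. Its direction depends on retention nobody has yet observed.
- That removing a few participants would by itself move the result. Step 5 shows a small effect when those removed still vape.

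The reply does not dispose of the point. The model and covariates protect only under missing at random, and cannot recover the outcomes of people with no follow-up whose continued vaping drove them out. A check of attrition by arm shows that dropout differs, not whether it depends on outcome. The restriction to those retained is something the article states, not a detail left to another document.

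**Conclusion.** The point holds in this form. The self-report analysis is defined on a set formed after randomisation, that definition does not fit the imputation rule, and the rule depends on an undefined judgement of negligibility. Verified abstinence is affected through the shared method and rule, not through the restriction itself. One removal route after allocation, disqualification for group content, is specific to the intervention arm.

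In size, the assumed scenarios produce spurious risk ratios of 1.21 to 1.33 and 0.8 to 1.3 percentage points at a 3.2% rate. They rest on unequal dropout and on every dropout vaping, neither of which the article quantifies. The 3.2% and 8.3% are verified rates from the earlier Facebook trial, so they do not describe self-report here. In illustration A the ratio does not depend on them, but the absolute differences scale with the base rate.

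**What to change.** - Replace the restriction to those retained with all randomised participants in their allocated arm, for both the self-report and the verified analyses. This also reconciles Data analysis with Primary analysis.
- Apply multiple imputation in every case, without the negligibility condition.
- Add a prespecified sensitivity analysis that counts missing as vaping, for both outcomes.
- State that participants disqualified from the study stay in the analysis set. This concerns the analysis only, not when disqualification is appropriate.
- Complete authenticity checks before allocation is released, or judge them blind to arm using pre-randomisation data only.

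The cost is mainly wording. Headline abstinence rates will be somewhat lower than among those retained. Finishing the checks first means a short hold between the baseline survey and release of allocation, although intervention groups already start only about two weeks after their first member enrols.
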